## Abstract

**Background:**

Emotional dysregulation (ED) constitutes a relevant factor involved in the onset and maintenance of many mental disorders. Targeting ED during adolescence could be a determinant both to identify high-risk individuals and to promote preventive interventions. This study will aim to evaluate the impact of a brief Dialectical Behavioral Therapy (DBT)-based intervention for adolescent students by measuring changes in emotional regulation skills and impulsive behaviors. Moreover, alterations in biological features related to stress response and inflammation will be assessed as potential biological variables associated with ED.

**Methods:**

This is a randomized trial. A total of 20 classes of adolescent students will be recruited among high schools in Brescia, a city in northern Italy. They will be randomized to the psychoeducational intervention (experimental group) or to a control condition (control group). The intervention will be based on DBT Skills Training for Emotional Problem Solving for Adolescents, and will consist of four monthly, 2-h sessions (for a total of 8 h) scheduled during regular school time. Participants will be assessed at baseline, post-intervention, and at 3 and 6 months of follow-up. The primary outcome measures will be represented by changes in the use of emotional regulation skills and by changes in the frequency of impulsive behaviors. Salivary samples will be collected at baseline and post-intervention to explore possible biological features underlying ED.

**Discussion:**

Data from the present project will offer the opportunity to better understand the complex phenomenon of ED. Repeated assessment will cover several domains (emotional, behavioral, social, biological) as potential factors associated with ED. Moreover, it will be possible to establish the effect of the proposed intervention, thus helping to improve knowledge on the impact of school-based universal preventive programs. Finally, the current trial will propose an integrated screening and intervention-based model. Ultimately, this could reduce barriers to youths’ mental health care by fostering collaboration between schools and mental health services.

**Trial registration:**

ClinicalTrials.gov NCT04349709. Registered on April 16, 2020.

## Administrative information

Note: the numbers in curly brackets in this protocol refer to SPIRIT checklist item numbers. The order of the items has been modified to group similar items (see http://www.equator-network.org/reporting-guidelines/spirit-2013-statement-defining-standard-protocol-items-for-clinical-trials/).

## Introduction

### Background and rationale {6a}

Adolescence is a critical period since most mental disorders develop before the age of 25 [1]. The Health Behavior in School-aged Children (HBSC) study prospectively assessed several aspects of the physical and psychological well-being of adolescent students from different countries [2]. Findings from the HBSC showed a small, linear increasing trend in psychological distress indices, especially in higher-income countries [3]. Of note, compared to other countries, Italy reports the highest rate of youths that refer to sadness, irritability, sleep problems, and psychosomatic health complaints [3].

The ability to regulate emotions represents a determinant variable and is strictly associated with the mechanisms involved in pursuing personal goals and establishing positive interpersonal relationships [4]. Difficulties in emotional regulation processes represent a relevant risk factor for the development of mental disorders [5, 6]. Emotional dysregulation (ED) is a multidimensional construct including different facets, such as a lack of awareness about experienced emotions, non-acceptance of emotional distress, impulsivity, the inability to pursue goals when emotionally distressed, and a lack of regulatory strategies [4]. ED embodies the core dimension of borderline personality disorder (BPD) and is mainly characterized by rapid and intense emotional changes, impulsive behaviors, and unstable relationships [7]. The reduced ability to regulate emotions denotes a relevant feature that can be observed in other mental disorders, such as depression and anxiety [8, 9], and with other clinical conditions, such as substance-related issues [10, 11], suicidal ideation [12], and self-harm [13]. Indeed, in the absence of more adaptive coping mechanisms, health-risk behaviors (e.g., self-harm, alcohol or substance abuse, risky sexual behaviors) are sometimes used to manage psychological distress [14, 15].

Since emotional regulation is a modifiable skill, interventions helping students to improve emotional regulation-related strategies could represent a promising primary prevention approach. Several studies support the use of socioemotional learning (SEL) as part of school educational programs [16, 17]. SEL programs aim to help children and adolescents acquire and practice the skills they need to successfully cope with stressful life events [16, 17]. A meta-analysis of SEL programs found that children and adolescents who participated in SEL programs showed better indicators of social-emotional skills and well-being than those who did not participate [18]. Adolescence is characterized by high emotional stress because of demands that typically occur during this period such as academic pressure, dating and intimacy issues, bullying, peer rejection, alcohol and drug use, concerns about physical attractiveness, and becoming more independent of one’s parents. Therefore, adolescents may have a particular need to regulate their emotions to face stressors and to carry out crucial steps involved in forming their identity and personality [19].

There are different kinds and formats of school-based interventions to strengthen emotional regulation in adolescents. Available studies reveal a positive effect on mental health and emotional regulation skills; in contrast, there is scant evidence about the impact on maladaptive behaviors. Moreover, most interventions are not manualized, and most existing studies are not based on sample size calculations, nor do they provide follow-up assessments. It is still not possible to draw any definitive conclusions regarding the superiority of one intervention over another. However, DBT has several values that support its application. First, it is in line with the SEL criteria [16]; moreover, it is manualized and includes a broad range of cognitive and behavioral techniques. Finally, this program can be conducted by schoolteachers who have received the proper training.

Dialectical behavioral therapy (DBT) is an empirically supported treatment rooted in the biosocial theory of ED [20]. The common underlying dysfunction in emotional regulation makes this treatment a valid transdiagnostic approach in clinical settings [21]. DBT was originally conceived for adults with BPD; subsequently, this treatment was adapted for adults with different psychiatric conditions [22–24], as well as for adolescent patients [21, 25, 26]. DBT skills encompass basic social and emotional life competencies; indeed, they are helpful for everyone and are useful in non-clinical populations such as school contexts [27]. DBT STEPS-A is the adaptation of DBT specifically designed for students in middle and high school. Studies evaluating the efficacy of DBT STEPS-A are ongoing; however, preliminary data support its use in schools. Indeed, positive results have been found with a selected population of students experiencing behavioral or academic challenges [28]. Recently, DBT has been applied as a universal program for the entire class, and students have exhibited improvement in social resiliency and emotional dysregulation [29].

Emotional regulation abilities develop substantially during adolescence, shifting from reliance on parental support to internal regulatory processes [30]; this transformation parallels the neurobiological changes in brain circuits involved in emotional processes [31]. It is well known that early traumatic experiences and stressful life events are strong risk factors for the onset of mental disorders [32], and individuals exposed to early traumatic experiences display difficulties in regulating their emotional responses [33]. Among the biological systems involved in the effect of stressful experiences on the vulnerability to develop ED and psychiatric disorders more generally, there is the hypothalamic-pituitary-adrenal (HPA) axis [34–36]. More specifically, exposure to early stressful life events may cause persistent alterations in the HPA axis’ functionality, leading to a persistent release of the stress hormone cortisol. Cortisol acts on its receptors, which are widely distributed in limbic brain regions, thus influencing stress response, cognition, affect, and behavior [34].

In line with this, in a sample of 180 adolescents at high risk for psychopathology, it was found that high morning cortisol levels predicted the onset of a major depressive episode in the following year [37]. Another, similar study indicated that high morning saliva cortisol levels predicted the development of depressive symptoms by the age of 16 in 13-year-old adolescents [38]. However, although the presence of alterations in cortisol release and depression is well established, weaker outcomes are found in the context of anxiety disorder or externalizing disorder. Indeed, some authors did not find an association between cortisol and psychopathology, or discovered an association in a different direction than expected [39, 40]. The age and severity of symptoms constitute relevant factors for HPA axis functioning, thus contributing to explaining the inconsistencies in the available evidence [39]. Moreover, the majority of the studies included adults.

Investigations with adolescents are needed to understand the exact nature of the relationship between the HPA axis and psychopathology. In this framework, the identification of biological variables linked to difficulties in emotional regulation in youths has been recognized as a relevant domain to identify possible factors of susceptibility to mental disorders [41].

### Objectives {7}

The aim of the present study is twofold. The first is to evaluate the impact of a school-based intervention focused on emotional regulation strategies in a sample of adolescent students. The primary outcome will be changes in the frequency of use of emotional regulation skills and changes in the frequency of impulsive behaviors. Our hypothesis is that (1) at the end of intervention, the students who received the intervention will report a reduction in the frequency of impulsive behaviors compared to baseline, whereas we expect no differences in the group of adolescents who will not receive the intervention; (2) at the end of intervention, the students will report an increase in the use of emotional regulation skills compared to baseline, while we expect no differences in the control group; and (3) these changes will be maintained at 3 and 6 months of follow-up.

The second aim was to assess the association between biological features and ED in adolescent students. Specifically, we will compare several biomarkers related to stress response and inflammation in subgroups of students with different levels of ED assessed with the Difficulties in Emotion Regulation Scale (DERS) [4] measured at baseline. Moreover, the repeated collection of salivary samples post-intervention will allow us to evaluate the role of these biological features in the interventions’ effects on the behavioral variables described above (i.e., impulsive behaviors and use of skills).

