### Outcomes {12}

#### Primary outcomes

##### Emotional regulation skills

DBT-Ways of Coping Checklist (DBT-WCCL) [45]

The DBT-WCCL is a 59-item self-report questionnaire measuring the frequency of DBT skills use (DBT Skills Subscale, 38 items) and dysfunctional coping strategies (Dysfunctional Coping Subscale, 21 items). Participants will be asked to indicate, on a 4-point Likert scale, the frequency of use of each skill in the previous month (i.e., never used, rarely used, sometimes used, or regularly used). The scale showed good internal consistency (Cronbach’s alpha coefficients for the subscales ranged from .84 to .96) and content validity [45]. For our primary outcome analysis, we will assess the difference between the two groups in terms of the proportion of participants categorized as “improved” post-intervention. Specifically, we will consider as “improved” those participants with a difference of at least one category, toward improvement, from the baseline to post-intervention in the frequency of use of functional skills. Intervention efficacy will be defined by a difference of at least 20% (i.e., 12/59 items) of improvement between groups after the intervention.

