##### Impulsive behaviors

Checklist for Impulsive Behaviors (CIB)

This CIB is an ad hoc 15-item checklist created to determine the frequency of impulsive behaviors: alcohol use (4 items), substance use (2 items), internet addiction (4 items), gambling (1 item), non-suicidal self-injury (2 items), unprotected sex (1 item), and binge eating (1 item). Participants will be asked to indicate, on a 5-point Likert scale, the frequency of impulsive behaviors that occurred in the previous month (never; only once a week; two or three times a week; at least 4 times a week). Moreover, the checklist includes a section to evaluate the lifetime frequency of each behavior on a 6-point Likert sale (1–2 times, 3–5 times, 6–9 times, 10–19 times, 20–39 times, at least 40 times). For our primary outcome analysis, we will assess the difference between the two groups in the proportion of participants categorized as “improved” at post-intervention. Specifically, we will consider as “improved” those participants with a difference of at least one category toward improvement from baseline to post-intervention in the frequency of impulsive behaviors. Intervention efficacy will be established by treatment success, defined as at least 13% (i.e., 2/15 item) between groups after the intervention.

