### Sample size {14}

The primary outcome measures will be represented by changes in impulsive behaviors (established by the Checklist for Impulsive Behaviors) and by changes in emotional regulation skills (determined by the DBT-Ways of Coping Checklist).

Precisely, the outcome will be evaluated in terms of change (pre/post) in percentage of “yes” answers in the two groups (treated and control), where “yes” is defined as a difference of at least one category toward improvement from baseline. More specifically, the scores of the Checklist for Impulsive Behaviors are measured on a Likert scale. Therefore, a “yes” answer implies a decrease in the frequency of impulsive behavior; for example, from the category “two or three times a week” to the category “one time a week.” In a similar manner, a “yes” answer for the DBT-Ways of Coping Checklist means a decrease in the use of dysfunctional skills; for example, from the category “regularly used” to “sometimes used,” or vice versa for functional skills.

We assumed that at baseline, there would be a between-group difference by chance of 7% (i.e., 1/15 yes answers, where 15 is the total number of checklist items) on the Checklist for Impulsive Behaviors and that this difference would increase by up to 13% (i.e., 2/15 yes answers) after the intervention. Based on these assumptions and applying a two-sided test for paired binomial proportions, with a significance level equal to 0.05 and a power of 0.8, the estimated sample size was *n* = 340 (170 per group). Moreover, considering a drop-out rate of 20%, the minimum sample size (MSS) reached *n* = 426 (213 per group).

In the same way, we assumed that on the DBT-Ways of Coping Checklist, there would be a difference by chance of 7% (i.e., 4/59 yes answers, where 59 is the total number of the checklist DBT items) at baseline, and that this difference would increase by up to 20% (i.e., 12/59 yes answers) after the intervention. This last hypothesis was made considering that, given the focus of treatment, we expected a greater change in emotional regulation skills than in dysfunctional behaviors. Based on these considerations and applying a two-sided test for paired binomial proportions, with a significance level equal to 0.05 and a power of 0.8, we reached an estimated sample size of *n* = 84 (42 per group).

In sum, due to both the outcome measures and related sample size estimations, the final sample size needed was 426 students.

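### Two primary outcomes are each sized at a full two-sided 0.05 and each carries its own definition of efficacy, but no rule says whether one or both must succeed

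*Protocol article*

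**What the plan says.** All references are to the protocol article.

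- **Objectives {7}:** "The primary outcome will be changes in the frequency of use of emotional regulation skills and changes in the frequency of impulsive behaviors". Separate numbered hypotheses follow for impulsive behaviours and for skills use.
- **Outcomes {12}, Emotional regulation skills (DBT-WCCL):** "Intervention efficacy will be defined by a difference of at least 20" per cent between groups.
- **Outcomes {12}, Impulsive behaviors (CIB):** "Intervention efficacy will be established by treatment success, defined as at least 13" per cent between groups. Neither definition refers to the other outcome.
- **Sample size {14}:** two separate calculations, each "applying a two-sided test for paired binomial proportions, with a significance level equal to 0.05 and a power of 0.8". CIB needs 340 (170 per group), or 426 with 20% drop-out. DBT-WCCL needs 84 (42 per group). The larger figure becomes the trial size. The section expects a larger change in skills than in behaviours.
- **Statistical methods {20a}:** names chi-squared tests and generalised mixed models, with no significance level, order of testing or multiplicity rule.

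**The concern.** The plan allocates 0.05 twice and defines efficacy twice. Anyone applying the two efficacy definitions as they stand could claim that the intervention works on the strength of one significant outcome, whichever it was. The error rate for that overall claim is then not held at 5%.

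There is also a practical gap. Because the authors expect unequal effects, a split result (skills significant, impulsive behaviours not) is foreseeable, and the plan does not say what the trial would then conclude. If the rule is chosen after the data are seen, it protects nothing.

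**Working it through.** **1. Is each outcome really sized at the full 0.05?** The inputs are the stated proportions, 7% to 13% for CIB and 7% to 20% for DBT-WCCL, with power 0.80. The formula that reproduces the plan's figures is

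n = [z(1−α/2)·√(p0(1−p0)) + z(0.80)·√(p1(1−p1))]² / (p1−p0)²

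- CIB, α = 0.05: (1.960×0.2551 + 0.842×0.3363)² / 0.06² = 170.35; stated 170 per group.
- DBT-WCCL, α = 0.05: (1.960×0.2551 + 0.842×0.4)² / 0.13² = 41.4, rounded up to 42; stated 42 per group.
- Drop-out: 170/0.8 = 212.5, rounded up to 213 per group, 426 in all; stated 426.

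At α = 0.025 the same formula gives 203.03, so 204 per group for CIB (408 in all; 408/0.8 = 510), and 49 per group for DBT-WCCL. The stated sizes therefore reserve no alpha. A 510-student requirement would also exceed the 440–460 students expected under Study setting {9}.

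**2. Error if significance on either outcome suffices.** With no effect on either outcome, two-sided family-wise error = 1 − P(|Z1| < 1.96, |Z2| < 1.96). For independent tests this is 1 − 0.95² = 9.75%. Counting only rejections that favour the intervention, it is 1 − P(Z1 < 1.96, Z2 < 1.96); for independent tests, 1 − 0.975² = 4.94%. The correlation is not given, so a range is shown.

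| Correlation of test statistics (assumed) | Two-sided family-wise error | False claim of benefit (single test 2.5%) |
|---|---|---|
| 0 | 9.75% | 4.9% |
| 0.3 | 9.5% | 4.8% |
| 0.5 | 9.1% | 4.5% |
| 0.7 | 8.3% | 4.2% |

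**3. Error if both must succeed.** It is at most 5% without adjustment. By the plan's own formula, power at 170 per group is 79.9% for CIB and 99.9% for DBT-WCCL, so joint power is still about 80%. The sample size does not show which rule was meant.

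**4. Error if the observed 20% and 13% differences are the rule.** Take 170 per group, no clustering and a common improvement rate p (assumed, 7% to 50%). SE = √(2p(1−p)/170). At p = 0.5, SE = 0.0542. CIB: 0.13/0.0542 = 2.40, giving 0.83%. DBT-WCCL: 0.20/0.0542 = 3.69, giving 0.01%. Together this is about 0.8%, falling to practically zero at p = 0.07. Clustering raises it: at an assumed intraclass correlation of 0.05 with 17 analysed per class (340/20), the design effect is 1 + 16×0.05 = 1.8 and the figure at p = 0.5 is about 4.0%.

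**5. Power under the candidate rules.** Because the outcome is compared between groups, I used the two-group formula at 170 per arm:

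power = Φ{[|p1−p0|√n − z(1−α/2)√(2p̄(1−p̄))] / √(p0(1−p0)+p1(1−p1))}

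CIB (7% v 13%): 45.4% at α = 0.05, 34.5% at 0.025. DBT-WCCL (7% v 20%): 94.3% and 90.1%. For independent tests:

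- Fixed sequence, DBT-WCCL then CIB: CIB power 0.943×0.454 = 42.7%; skills 94.3%.
- Holm: CIB power 0.345 + (0.454−0.345)×0.901 = 44.3%; skills 0.901 + (0.943−0.901)×0.345 = 91.6%.

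At an assumed intraclass correlation of 0.02 (design effect 1.32, effective 128.8 per arm), CIB power is 34.0% under Holm and 31.3% under the fixed sequence. At correlations of 0.5 to 0.7 between the tests, the two are about equal for CIB. The drop to 34.5% belongs to a fixed 0.025 split, not to Holm.

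**The case against.** A reader might infer that the protocol lets either outcome establish efficacy alone, and that the chance of a false efficacy claim is therefore 9% to 10%. The documents do not support that as stated, for four reasons.

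- **No either/or rule is written.** Objectives {7} joins the two changes with a conjunction under a single primary outcome, and the trial is sized to the more demanding outcome, which suits a both-required reading equally well. This stands. But no both-required rule is written either, and the two efficacy definitions are free-standing, so the either-outcome reading is a fair one.
- **Efficacy is worded as a size of difference, not as p < 0.05.** This stands as a limit on the figures: under that reading step 2 does not apply. It sits badly with the Sample size section, however. A true difference equal to the threshold would be observed at or above it only about half the time, so a stated power of 0.8 would have no meaning for such a rule.
- **The 8% to 10% range counts rejections in both directions.** This also stands. False claims of benefit are 4.2% to 4.9% over the same correlations; the near-doubling remains at low to moderate correlation.
- **The analysis plan is not shown and may settle the rule.** It may, and the absence of multiplicity detail from a journal article is not in itself the point. What the article does fix is two full allocations of 0.05 and two separate efficacy definitions, and a later alpha split would contradict its own sample size.

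**Conclusion.** The concern holds in a conditional form. The protocol fixes two primary outcomes at two-sided 0.05 each and defines efficacy on each alone, without saying how the two combine. If significance on either supports a claim, the two-sided family-wise error is about 8% to 10% for correlations from 0.7 down to 0, and false claims of benefit occur about 4% to 5% of the time against 2.5%.

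This rests on three assumptions: that one outcome suffices, that significance decides, and that each test is valid for class-randomised data. Tests that ignored class would inflate each outcome's error separately, which is a different matter. The defect is an unstated decision rule, not a demonstrated inflation: under a both-required rule the error is at most 5% as the plan stands.

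**What to change.** State one decision rule, in the same words, in Objectives {7}, in both primary-outcome descriptions and in Sample size {14}. Say that efficacy is claimed only under that rule, with overall two-sided error 0.05, and say what part the 20% and 13% differences play in it. Any of three rules would do:

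- **Holm across the two outcomes.** CIB power is about equal to or slightly above the fixed sequence, and CIB can still be claimed if skills fails. Skills power falls a little (94.3% to 91.6% in the working above).
- **Fixed sequence, DBT-WCCL skills at 0.05, then CIB at 0.05.** This follows the protocol's expectation of a larger effect on skills and keeps full skills power, but gives up any CIB claim if skills fails.
- **Both required**, if that was the sponsor's intention. No alpha adjustment is needed; a split result is then not a success.

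The cost is one sentence and a small loss of power, with no extra students or data. The choice should be recorded before any outcome data are examined by arm.
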